**Figure 3 F3:**
[figure not shown]
Flowchart of the study phases. T1 = time 1, T2 = time 2, T3 = time 3, T4 = time 4, T5 = time 5, TTR = time in therapeutic range.

We will collect the following data:

(i)sociodemographics: age, sex, family income, cognitive status, dependence on activities of daily living (ADL), religiosity, alcohol consumption, and smoking habits;(ii)clinical data: indication for warfarin use, INR target, type and number of comorbidities, number of missing appointments, stroke history;(iii)laboratorial data: INR values; and(iv)information on drug therapy: number of concomitant drugs used chronically, assistance with taking warfarin or other prescribed medications, warfarin dosage changes, complexity of drug therapy, and modifications in concomitant medications.

### Sample size

2.5

Sample size was calculated using diggle.linear.power function of longpower package in the software R 3.4.4 version.^[21]^ The TTR will be prospectively assessed, from T0 to T5. We considered an absolute increase of 6% in TTR with standard deviation of 7.5,^[22]^ 80% power, level of significance of 0.05 and at least 15% of variation in the slope coefficient between intervention and control groups. The calculated sample was 71 individuals for each group, and we planned to include 20% additional patients to account for a follow-up loss, resulting in 85 individuals allocated in each group. Also, we used composite symmetry autocorrelation structure with a correlation of 0.80 between the times of data collection.

### Recruitment

2.6

Before recruitment, all patients assisted between August 2017 and September 2017 at the studied ACs (n = 1371) had their TTR calculated to identify those presenting TTR <60%. A new TTR calculation occurred between July and December 2018 to certify if patients with low TTR (<60%) identified in the first screening would continue to fulfill inclusion criteria. Thus, patients with persistently low TTR will be invited to participate in the study. To complete the sample, new patients with low TTR between July and December 2018 will be considered for inclusion in the study. Recruitment phase started in January and is expected to end by May. Patients’ invitation is planned to take place before or after scheduled appointments for monitoring oral anticoagulation.

Validated instruments translated into Brazilian Portuguese will be used. The Duke Religious Index (DUREL) has 5 items assessing 3 of the religiosity dimensions most related to health outcomes: organizational religiosity (OR), non-organizational religiosity (NOR) and intrinsic religiosity (IR). Scores (OR, NOR, and IR) are evaluated separately and they cannot be used as a total score.^[27]^ Katz scale consists of 6 items that measures the individual performance on self-care activities, according to a complex hierarchy: nourishment, sphincter control, transference, personal hygiene and ability of get dressed and taking baths, to identify dependence level on ADL.^[28]^ Mini-Mental State Examination (MMSE) is divided into 2 sections. The first one requires only vocal answers and includes orientation, memory, and attention with the highest score of 21. The second section tests ability to nominate, to follow verbal and written commands, to write a phrase and to copy a polygon with the highest score of 9.^[29,30]^ Short Assessment of Health Literacy for Portuguese-speaking Adults (SAHLPA-18) contains 18 items allowing the classification of participants as having inadequate or adequate health literacy with scores of 0 to 14 or 15 to 18, respectively. Participants are invited to read out loud 18 medical terms and to associate them to 1 of 2 words present to the participant.^[31]^ At last, the Medication Regimen Complexity Index (MRCI) is a specific, reliable and valid tool used to measure the complexity of pharmacotherapy.^[32]^

### Data management

2.8

Identification of participants will be coded. The results from the surveys application and from the examination of charts data will be registered in worksheets and will be under the responsibility of the researcher responsible for the research. Database will be validated by double typing using Epi Data, 3.1 software.

### Statistical analysis

2.9

TTR will be calculated by the Rosendaal method using a linear interpolation of INR results. TTR will be calculated at least 2 INR measurements. For participants who had INR intervals higher than 56 days, we used INR values to calculate TTR for the valid intervals (<56 days) and afterward we used the independent TTR values to calculate the final TTR by the arithmetic mean.^[33]^

Categorical variables will be expressed as frequency and percentage. Symmetric continuous variables will be expressed as means and standard deviation while asymmetric data will be expressed as median, first quartile, and third quartile.

To evaluate significance of each variable in the outcomes, univariate models will be adjusted using generalized estimation equation (GEE) with appropriate distribution for each outcome (normal or gamma distribution for TTR and binomial distribution for knowledge and adherence). Wald tests will be performed for each variable coefficient using an initial significance level of 0.20. All variables identified as initially significant will be added to a multivariate model and significance level will be set at 0.05. One final GEE multivariate model will be presented for each outcome including exclusively significant coefficients. Post hoc analysis will include comparisons of outcome means (or probabilities) at different time points. Statistical analysis will be performed in R version 3.4.4.

Patient refusal, death or other situations that would make it difficult for the patient to continue in the study will be registered and they will be considered as an intention to treat for analysis. Important protocol modifications will be reported to REBEC.

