**Methods::**

Patients ≥18 years with AF, on warfarin for at least 6 months and time in therapeutic range (TTR) <60% will be recruited at 2 anticoagulation clinics (ACs) in Brazil. Patients from 1 AC will be allocated to the intervention group and patients from the other AC will be allocated to the control group. Intervention group will attend educational sessions based on a patient-centered care approach, and the control group will receive usual care. The intervention will be based on Paulo Freire's theory and tailored according to practices involving health empowerment and techniques applied to individuals with limited socioeconomic status. The intervention is estimated to last 5 months. We will consider TTR as the primary outcome and knowledge and self-reported non-adherence to warfarin therapy as secondary outcomes. TTR values and non-adherence will be measured before intervention (T0) and at times immediately after (T1), and 3 (T2), 6 (T3), 9 (T4), and 12 (T5) months after intervention. Knowledge will be measured at times T0, T1 e T5. The calculated sample size indicated 85 patients in each group.

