### Study setting

2.1

This is a non-randomized controlled clinical trial to be conducted at 2 public university hospitals in Belo Horizonte, a 3.5-million-inhabitant city in Southeast Brazil. Patients will be recruited at 2 anticoagulation clinics (ACs) from the hospitals Hospital das Clínicas da UFMG (HC-UFMG) and Hospital Risoleta Tolentino Neves (HRTN). Patients from the former AC will be allocated to the intervention group and patients from the latter AC will be allocated to the control group.

These study settings are tertiary referral hospitals. More than 90% of patients perform INR at the hospital laboratory. Those ACs are multidisciplinary with a team composed by physicians, pharmacists, and nurses. Specialized care is regularly provided to outpatients who receive education and warfarin dose adjustments. Both ACs have similar anticoagulation protocols to guide professionals to perform standardized care practice. The trial has been registered on Registro Brasileiro de Ensaios Clínicos (REBEC) (http://www.ensaiosclínicos.gov.br). We followed the SPIRIT recommendations to describe the study protocol.^[15]^

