### Outcomes

2.4

The primary outcome will be the oral anticoagulation control, assessed by TTR. We will consider as secondary outcomes knowledge on warfarin therapy and self-reported adherence to oral anticoagulation.

The outcomes will be compared intra and intergroups, using pre-defined time points to measure outcomes before and after the intervention. TTR and self-reported adherence to warfarin therapy will be measured 6 months before starting the intervention (T0), immediately after intervention completion (T1) and at 3 (T2), 6 (T3), 9 (T4) and 12 (T5) months after intervention completion. To prevent patients from exhaustion and considering that knowledge takes time to change, this variable will be measured at T0, T1, and T5 (Fig. 3).

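### Section 2.5 sizes the trial on a between-group difference in slope, but no test written in section 2.9 isolates the difference in change from T0 between the two non-randomised clinics

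*Protocol article*

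**What the plan says.** **Design (2.1 Study setting).** "This is a non-randomized controlled clinical trial to be conducted at 2 public university hospitals in Belo Horizonte". Group and clinic are the same variable: "Patients from the former AC will be allocated to the intervention group and patients from the latter AC will be allocated to the control group".

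**Powered contrast (2.5 Sample size).** "We considered an absolute increase of 6% in TTR with standard deviation of 7.5", together with "at least 15% of variation in the slope coefficient between intervention and control groups". A difference in slope is a group-by-time contrast.

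**Stated comparison (2.4 Outcomes).** "The outcomes will be compared intra and intergroups, using pre-defined time points to measure outcomes before and after the intervention". TTR and adherence are measured from T0 to T5, and knowledge at T0, T1 and T5.

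**Stated tests (2.9 Statistical analysis).** The chain has three steps:

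1. One-variable GEE models: "Wald tests will be performed for each variable coefficient using an initial significance level of 0.20".
2. A multivariate GEE of the variables that pass, tested at 0.05, with only significant coefficients retained in the model that is presented.
3. "Post hoc analysis will include comparisons of outcome means (or probabilities) at different time points".

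The section does not say how group and time enter any of these models.

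**The concern.** Without randomisation, no effect of the intervention does not imply equal TTR in the two clinics. It implies only that a difference present at T0 persists. Capping entry at TTR below 60% limits the range in both clinics but does not equalise their means.

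Two quantities can be read off the written chain as between-group tests: a coefficient for group, and a comparison of the groups' means at a given time. Both contain the clinics' starting difference. A constant difference, visible at T0 and removable with data already collected, could therefore be reported as an effect or could cancel a real one. The retention rule adds a further risk: if a lower start in the intervention clinic shrinks the group coefficient, group can fall out of the model, and the primary outcome would then have no reported between-group estimate. Knowledge and adherence go through the same chain.

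**Working it through.** **Inputs from the article.** SD 7.5, correlation 0.80 under compound symmetry, 71 evaluable patients per group, level 0.05 (taken as two-sided; the article does not say) and a 6-point effect, all from 2.5. Six occasions, T0 to T5, from 2.4.

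**Assumptions.** A constant clinic difference d of 1.5, 2.25 or 3 points (0.2, 0.3 or 0.4 SD); the article gives no figure. Any effect is fully present from T1 to T5.

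**The plan's own figure.** The 85 follows from 71 × 1.2 = 85.2. The 71 does not follow from a natural reading of the inputs. The slope formula is n = 2(1.960 + 0.842)²σ²(1 − ρ) / (Σ(t − t̄)² δ²). With visits coded 0 to 5 (sum of squares 17.5) and δ = 6/5 per visit, it gives 2 × 7.85 × 56.25 × 0.2 / (17.5 × 1.44) = 7 per group. With 15% of that slope it gives 7.008 / 0.15² = 311.5, or 312. That is a separate matter. I take 71 as given, because the question here is which contrast is tested.

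**Standard errors.**

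- Means at one time: 7.5 × √(2/71) = 1.259.
- Group coefficient pooled over T0 to T5: 1.259 × √((1 + 5 × 0.8)/6) = 1.149.
- Difference in change, T5 minus T0: 1.259 × √(2 × (1 − 0.8)) = 0.796.

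**Rejection.** P(|Z + shift/SE| > 1.96). The shift is d + effect for T5 means, d + (5/6) × effect for the pooled coefficient (T0 carries no effect), and the effect alone for the change contrast.

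| No intervention effect | d = 1.5 | d = 2.25 | d = 3 |
|---|---|---|---|
| T5 means | 22% | 43% | 66% |
| Pooled group coefficient at 0.05 | 26% | 50% | 74% |
| Difference in change from T0 | 5% | 5% | 5% |

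For example, at d = 3 the pooled ratio is 3/1.149 = 2.61, which gives 74%.

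**True 6-point effect, intervention clinic starting 3 points lower.**

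- Pooled coefficient: shift −3 + 5 = 2, ratio 2/1.149 = 1.74, power 41%. It passes the 0.20 screen (critical value 1.28) with probability 68%, so group fails the screen in 32%, about one time in three.
- T5 means: shift 3, ratio 3/1.259 = 2.38, power 66%.
- Difference in change: 6/0.796 = 7.5, power above 99%.

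**Simulation check.** An exchangeable GEE, 400 trials per scenario, gave 75% for the pooled coefficient at d = 3 with no effect, and 44% at d = −3 with a 6-point effect. The change contrast (mean of T1 to T5 minus T0) rejected in 4% to 6% under no effect.

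**Does the second stage repair this?** Adding categorical time as a main effect does not: at d = 2.25 with no effect, group was still rejected in 47% of 200 simulated trials. Covariates help only as far as they explain the clinic difference. If they removed half of a 3-point difference, 1.5 points would remain and rejection would be about 26%.

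**T0 as a covariate.** Regressing T1 to T5 on T0 subtracts only ρd, which leaves a bias of (1 − 0.8)d = 0.2d. At d = 3 this is 0.6 points against an SE of about 1.259 × √(1 − 0.8²) = 0.755, and false rejection at T5 is about 12%.

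**The case against.** A reader might infer that the plan tests TTR levels instead of change. The article does not go that far. It never writes a model with group alone as a main effect over T0 to T5; that is inferred from the description of one-variable models. Nothing in 2.9 excludes a time or group-by-time term, and 2.5 (slopes) and 2.4 (before and after, within and between groups) suggest that change was intended. The sentence on time-point means can also be read as contrasts across time, such as T1 against T0. The article is a condensed account, and detail of model terms often sits elsewhere. All of this stands against calling the analysis a demonstrated wrong test.

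Nor do the documents support treating the quoted Wald test as the final one. It is a 0.20 screen, and the decisive test is the multivariate coefficient at 0.05. The pooled figures at 0.05 are therefore an illustration, before covariates that might absorb part of a clinic difference. The size of any such difference is unknown. The clinics share an entry threshold and use similar anticoagulation protocols, and a constant difference would also be visible at T0 in the same output.

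The objection does not remove the mismatch. The article is not merely silent: it fixes tests, thresholds and a retention rule, and none of those steps yields the contrast that 2.5 sizes the trial on. Within-group before-after tests set beside between-group comparisons of means do not supply a difference in change.

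**Conclusion.** The point holds as a mismatch between the contrast that is powered and the tests that are written, and section 2.9 should be amended. Followed as written in a design where group equals clinic, the chain can let a constant clinic difference pass as an effect or hide one, and the selection steps can remove group altogether.

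The calculated size rests on the sponsor's SD, correlation and 71 per group, on assumed clinic differences of 1.5 to 3 points, and, for the pooled figures, on a group main effect tested at 0.05 without covariates. If the clinics happen to start level, false rejection stays at its nominal rate.

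**What to change.** In 2.9, for TTR, knowledge and adherence:

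- Force group, categorical time and group-by-time into the GEE, exempt from both the 0.20 and the 0.05 selection steps.
- Define the intervention effect as the between-group difference in change from T0, and base all between-group statements on it. State the scale on which it is expressed, since 2.9 allows normal, gamma and binomial models.
- Report time-point means and probabilities descriptively.

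Do not offer T0 as a covariate as an equivalent alternative. With non-randomised groups it leaves part of a baseline clinic difference in the estimate.

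The cost is wording only. T0 is already planned for all three outcomes, so no patients or measurements are added. A patient without a T0 value contributes little to the contrast, but entry already requires a TTR.

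The limit should be stated alongside the change. It removes constant clinic differences only. With one clinic per arm, and patients selected on low TTR, differing trends or differential regression to the mean remain confounded with the intervention.

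### The covariate procedure in section 2.9 yields no covariate-by-time terms, so the between-group difference in TTR slope is left essentially unadjusted for baseline factors that drive TTR change

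*Protocol article*

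**What the plan says.** All places are in the protocol article.

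- **Design** (2.1 Study setting): "This is a non-randomized controlled clinical trial to be conducted at 2 public university hospitals". One clinic supplies the intervention group and the other the control group.
- **Contrast the trial is sized on** (2.5 Sample size): "Sample size was calculated using diggle.linear.power function of longpower package in the software R 3.4.4 version", a function that compares two slopes. The inputs are "We considered an absolute increase of 6% in TTR with standard deviation of 7.5", "80% power, level of significance of 0.05", a compound-symmetry correlation of 0.80, and "at least 15% of variation in the slope coefficient between intervention and control groups".
- **Adjustment** (2.9 Statistical analysis): univariate GEE models come first, and "Wald tests will be performed for each variable coefficient using an initial significance level of 0.20". Then "All variables identified as initially significant will be added to a multivariate model and significance level will be set at 0.05". The final model for each outcome keeps only the significant coefficients. TTR may be modelled as normal or gamma, and no link is named.
- **Covariates** (2.4 Outcomes, data list): mostly fixed patient characteristics, such as "age, sex, family income, cognitive status, dependence on activities of daily living (ADL), religiosity". Health literacy and regimen complexity are measured as well (2.7). A few items can vary over time, such as dose changes and changes in concomitant drugs.

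Section 2.9 names neither a group-by-time term nor any covariate-by-time term.

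**The concern.** Patients are allocated by clinic, so the multivariate GEE is the plan's statistical means of handling measured differences between the two clinics' patients. The covariate step tests whether a variable is associated with TTR, which is an association with its level. The sized effect is a difference in how TTR changes over time.

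A variable that shifts a patient's TTR equally at every visit has no bearing on that patient's slope. A variable that alters the course of TTR does, and the procedure as written neither screens for that nor creates the term that would adjust for it.

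The article gives reason to expect such variables. It links low TTR to family income and health literacy, argues that patients with inadequate literacy stand to gain most from education, and deliberately includes patients with low literacy or cognitive impairment. If such a factor is more common in one clinic, a false intervention effect could appear, or a true one be hidden, in a result that readers will take as adjusted.

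**Working it through.** **1. The plan's own figure.** The slope formula is n = 2(z₀.₉₇₅ + z₀.₈₀)² v / d², with v = σ²(1 − ρ) / Σ(t − t̄)².

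- From 2.5: σ = 7.5, ρ = 0.80, 80% power, significance level 0.05 (two-sided is assumed).
- Assumed, because the article does not give them in this form: t = 0, 1, 3, 6, 9, 12 months and d = 0.15 TTR points per month.
- t̄ = 31/6 = 5.167; Σ(t − t̄)² = 271 − 31²/6 = 110.83.
- v = 56.25 × 0.20 / 110.83 = 0.1015.
- n = 2 × 7.849 × 0.1015 / 0.0225 = 70.8, so 71; then 71 × 1.20 = 85.2, so 85.

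Both stated sizes are reproduced, which supports reading the sized contrast as a slope difference.

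**2. Why a fixed main effect drops out.** With common visit times, complete data, identity link and exchangeable correlation, the group-by-time estimate equals the difference between groups in mean patient slope, bᵢ = Σ(tⱼ − t̄)yᵢⱼ / Σ(tⱼ − t̄)². A term γxᵢ adds γxᵢ Σ(tⱼ − t̄) / Σ(tⱼ − t̄)² to bᵢ. Since Σ(tⱼ − t̄) = 0, it adds nothing. The same holds for a group contrast in T5 minus T0.

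**3. Check by GEE fits** (85 per group, six times; assumed: x is 0.5 SD higher in the intervention clinic and changes the slope by 0.2 points per month per SD; group slope difference free of x is 0.25).

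| Setting | Unadjusted | x as main effect | x and x-by-time |
|---|---|---|---|
| Identity, complete, mean of 200 datasets | 0.356 | 0.356 (largest difference 8e-16) | 0.254 |
| Identity, x affects level only, mean of 200 | 0.255 | 0.255 | 0.254 |
| Identity, dropout, mean of 200 | 0.358 | 0.358 (largest change 0.014) | 0.258 |
| Gamma, log link, one dataset | 0.00659 | 0.00682 | 0.00400 |

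The second row matters: a factor that affects only the level does not confound the slope. In one complete identity-link dataset the group coefficient at t = 0 moved from 2.56 to −1.11 when x was added, so main effects do adjust differences in level.

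**4. Size, on assumed inputs.** A yes/no factor lowers the 12-month gain by 5 points (5/12 = 0.4167 per month); no true effect; 71 per group; complete data. Let p₀ and p₁ be its prevalence in the two clinics.

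- False slope difference: 0.4167 × (p₁ − p₀).
- Its standard error without the covariate-by-time term: √{[2v + 0.4167² (p₀(1 − p₀) + p₁(1 − p₁))]/71}.
- False-positive rate: Φ(z − 1.96) + Φ(−z − 1.96), where z is the difference divided by its standard error.

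| p₀ vs p₁ | False difference over 12 months | Per month / SE | z | False-positive rate |
|---|---|---|---|---|
| 30% vs 60% | 1.5 points | 0.125 / 0.0629 | 1.99 | 51% |
| 30% vs 50% | 1.0 point | 0.0833 / 0.0631 | 1.32 | 26% |
| 30% vs 40% | 0.5 point | 0.0417 / 0.0629 | 0.66 | 10% |

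Simulation of 5,000 datasets per row, using per-patient slopes, gave 51%, 27% and 10%. With the factor in the slope model the mean false difference was within 0.01 point of zero and the rate was 4% to 5%.

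**5. Scale.** The assumed 0.15 points per month is 0.15 × 12 = 1.8 points over 12 months. Against the 6-point increase named in 2.5, the largest false difference is 1.5/6 = 25%.

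**The case against.** The strongest reply is that section 2.9 nowhere says main effects only. It is silent on every model term, including group-by-time, and an article may leave interactions to the full plan. A reader might infer that the plan rules out covariate-by-time terms; the text does not support that. What stands against the reply is that 2.9 does state a procedure: one coefficient test per variable, joint entry, retention by significance. An analyst following it would not arrive at covariate-by-time terms.

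A reader might also infer that adjustment cannot change the slope contrast at all. That is too strong. Exact cancellation needs fixed covariates, an identity link and complete data. Time-varying covariates can move the estimate: in one dataset it went from 0.320 to 0.214. But dose and co-medication changes that arise after baseline may themselves be affected by the intervention, so they do not substitute for baseline adjustment.

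Nor do the documents support calling the slope contrast fully confounded. Only factors that are both imbalanced and related to TTR change matter, and within-patient change already removes fixed differences in level. The article describes two public university hospitals in one city with similar anticoagulation protocols. No passage gives a 30-point imbalance or a 5-point effect, and at 30% against 40% the distortion is modest.

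Finally, with one clinic per arm, no patient-level term removes confounding by clinic. That is correct and limits what the fix can achieve.

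**Conclusion.** The point holds in limited form. The stated covariate procedure does not match the contrast the trial is sized on. Followed as written, it leaves the estimate of TTR change essentially unadjusted for baseline patient factors that differ between the clinics and influence change, while it does adjust differences in level. The result is exact under a normal identity-link exchangeable GEE with complete data, and close to exact in the dropout and gamma log-link fits that were tried.

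The size is unknown from the documents. The range of about 0.5 to 1.5 points, with false-positive rates of about 10% to 50%, rests on the assumed prevalences and the assumed 5-point effect. The 1.8-point yardstick also rests on an assumed slope. The absence of covariate-by-time terms is inferred from the procedure described and is not an explicit statement of the plan. It is worth correcting because the remedy is cheap and uses data already collected.

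**What to change.** In section 2.9, state that the model includes a group-by-time term. Fix in advance a short list of baseline confounders already collected, for example age, family income, health literacy, cognitive status and regimen complexity. Enter each with a covariate-by-time (or covariate-by-pre/post) term, kept whatever its p-value. Equivalently, regress each patient's TTR change or slope on group plus these baseline variables. Report the adjusted group difference in change beside the unadjusted one. State as a limitation that differences between the two clinics themselves remain inseparable from the intervention.

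Cost: a few sentences, no new data, and a few degrees of freedom. If a single covariate turns out to be irrelevant to change, the standard error grows by about 1/√(1 − r²), where r is its correlation with group. For prevalences of 30% against 60%, r² = (0.5 × 0.3)² / (0.45 × 0.55) = 0.091, a rise of about 5%. For 30% against 40%, r² = (0.5 × 0.1)² / (0.35 × 0.65) = 0.011, a rise of under 1%. Several covariates together would cost somewhat more, which is why the list should be short.

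### The final model for every outcome keeps only significant terms and protects none, so the group and group-by-time terms and measured confounders can all drop out of a non-randomised comparison

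*Protocol article*

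**What the plan says.** Protocol article, section 2.9 (Statistical analysis), sets out a three-step rule.

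- Screening, in one-variable GEE models: "Wald tests will be performed for each variable coefficient using an initial significance level of 0.20".
- Retention: "All variables identified as initially significant will be added to a multivariate model and significance level will be set at 0.05".
- Presentation: "One final GEE multivariate model will be presented for each outcome including exclusively significant coefficients".

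The rule applies to TTR, knowledge and adherence alike. The only other comparison in the section is this: "Post hoc analysis will include comparisons of outcome means (or probabilities) at different time points".

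Section 2.1 (Study setting) describes the design: "This is a non-randomized controlled clinical trial to be conducted at 2 public university hospitals". One clinic supplies each arm: "Patients from the former AC will be allocated to the intervention group", and the second clinic supplies the controls. Section 2.4 (Outcomes) promises comparisons within and between groups at the set time points, and lists the baseline variables to be collected. Section 2.5 (Sample size) bases the trial on a between-group difference in slope from T0 to T5, with 80% power and a significance level of 0.05.

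**The concern.** The quantity that the sample size is built on, a difference in slope between the groups, is a group-by-time term. The analysis section never names that term or the group term, and its rule for the final model removes anything non-significant. A one-variable screen also has no natural place for an interaction. Applied as written, the rule lets the effect that the trial exists to estimate leave the final model. If it stays, it has been kept because it was large enough to pass a test.

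Confounders raise a second problem. With one clinic per arm and no randomisation, adjustment for measured patient differences is the part of the between-clinic threat that analysis can address. Confounding depends on imbalance between clinics as well as on association with the outcome. A rule that looks only at the p-value for the outcome association will discard variables that jointly carry bias. The p-values in the final model are then read as if no selection had taken place.

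**Working it through.** **The plan's own figures.** The plan gives no number for the selection rule. The nearest figures are the sample sizes. The step from 71 to 85 is 71 × 1.2 = 85.2. The 71 cannot be uniquely reproduced, because the text does not determine the time scale or the slope difference given to the function. It is not called wrong here, and nothing below depends on it except the planned power of 80%.

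**Check 1: how often the intervention term leaves, and what selection does to its estimate.**

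Inputs: screening level 0.20 and retention level 0.05 (section 2.9); power 80% (section 2.5). Assumptions: the term is among those screened, it is tested by a single two-sided Wald test (the protocol does not state sidedness), and the same statistic is used at both steps.

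Let δ = 1.960 + z(power), and let the Wald statistic be normal with mean δ and variance 1.

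- Chance of leaving at 0.05: Φ(1.960 − δ) − Φ(−1.960 − δ).
- Mean retained estimate divided by truth: 1 + [φ(1.960 − δ) − φ(1.960 + δ)] / [δ × P(retained)].

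At 80% power, δ = 1.960 + 0.842 = 2.802. The chance of leaving is Φ(−0.842) = 0.20. The ratio is 1 + 0.280 / (2.802 × 0.80) = 1.12.

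At 50% power, δ = 1.960. The chance of leaving is 0.50. The ratio is 1 + 0.399 / (1.960 × 0.50) = 1.41.

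| Power | δ | Leaves at 0.05 | Fails the 0.20 screen alone | Mean retained estimate / truth |
|---|---|---|---|---|
| 90% | 3.242 | 0.10 | 0.025 | 1.06 |
| 80% | 2.802 | 0.20 | 0.064 | 1.12 |
| 50% | 1.960 | 0.50 | 0.248 | 1.41 |
| 30% | 1.436 | 0.70 | 0.436 | 1.80 |

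If the term is always kept, the chance of leaving is 0 and there is no selection on its significance.

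**Check 2: confounders chosen by significance.**

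This is an illustrative simulation with 1,500 runs per row, 71 patients per arm, one linear outcome and 10 independent covariates. The group term was always kept, so the results show covariate selection alone. Covariates were screened one at a time at 0.20 and then deleted backwards at 0.05. The comparator adjusts for all 10. There is no true effect. The imbalance (in covariate SD) and the covariate coefficients are assumptions and do not come from the documents. Bias is in residual SD.

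| Imbalance | Coefficient | Bias, selected | Bias, all kept | Rejections, selected | Rejections, all kept |
|---|---|---|---|---|---|
| 0 | 0.1 | 0.005 | 0.005 | 5.5% | 4.8% |
| 0 | 0.2 | 0.004 | 0.004 | 6.5% | 5.6% |
| 0.2 | 0.1 | 0.103 | 0.001 | 12.4% | 5.5% |
| 0.2 | 0.2 | 0.093 | 0.001 | 10.3% | 5.2% |
| 0.3 | 0.1 | 0.151 | −0.003 | 18.2% | 5.6% |
| 0.3 | 0.2 | 0.125 | −0.009 | 15.9% | 5.4% |

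Without imbalance, ignoring the selection costs little. With modest imbalance in the same direction across covariates, the selected model rejects a true null two to three times as often as the 5% level allows. Adjustment for the full set does not.

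**The case against.** The article does not list the group term among the screened variables, so the authors may intend to keep it. That is possible, but the text exempts nothing and restricts the final model to significant coefficients. This is a stated rule rather than a detail left to an analysis plan.

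Four stronger readings are tempting, and the document does not support them.

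- *A null intervention effect would go unreported.* Section 2.4 commits to between-group comparisons, and section 2.9 adds comparisons of means or probabilities by time point. A null result therefore has a route into the report. What is missing is a protected place for the effect in the main model.
- *Any retained estimate is inflated.* The inflation is an average over trials that reach significance. A given estimate may be too small.
- *The time-point comparisons will be a set of uncorrected tests.* The article is silent on multiplicity, which an article may leave to the analysis plan. The wording about post hoc comparisons can simply mean comparisons made after the model is fitted, since section 2.4 fixes the time points in advance.
- *The gamma option would break down on TTR values of zero.* Section 2.9 allows "normal or gamma distribution for TTR", so the normal model is already available. The documents give no count of INRs per window from which to judge how often zeros would occur.

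It is also fair to say that the sample-size section implies a primary contrast. That stands, and it shows what the analysis section should name.

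**Conclusion.** The point holds in this form: section 2.9 fixes a selection rule that protects no term and applies it to the primary outcome of a non-randomised trial with one clinic per arm.

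If the intervention contrast is screened, it leaves the final TTR model in about 20% of trials at 80% power and 50% at 50% power. The mean overstatement when it is retained is about 12% and 41% respectively. These figures rest on a single two-sided Wald test and on the stated power being real.

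The direction of the confounder problem does not depend on assumed values, but its size does: 10% to 18% false rejections under the assumed imbalances, against 5.2% to 5.6% with full adjustment. Without imbalance, selection alone moved the rate only to between 5.5% and 6.5%. No analysis of this design can separate the intervention from the clinic, so the defect is an avoidable bias on top of an unavoidable one.

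**What to change.** Replace the screening and retention rule in section 2.9 with one prespecified model per outcome.

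- The model always contains group, time, group-by-time and a fixed list of baseline confounders, all kept whatever their p-values. The list can come from variables already collected, for example age, sex, family income, health literacy, INR target and number of drugs.
- Name the group-by-time (slope) difference over T0 to T5 as the primary TTR contrast, so that it matches section 2.5, and state its time scale. An average difference over the post-intervention visits would not be the quantity that the trial was powered for.
- Report that contrast with its estimate and confidence interval whether or not it is significant.
- Make the time-point comparisons secondary. For knowledge, use T0, T1 and T5, the only times at which it is measured.

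The cost is one rewritten paragraph. It needs no new data and leaves the 71 and 85 per group unchanged. Intervals may be somewhat wider. In the simulation with a true effect of 0.48 residual SD, full adjustment rejected in 76.5% to 81.4% of runs without imbalance and in 68.6% to 75.3% with it. Selection rejected in 86.3% to 92.8% with imbalance, but with mean estimates of 0.57 to 0.64, so its apparent extra power comes from bias. The report should still say that clinic and intervention cannot be separated.
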